### Data analyses

Data will be analyzed using IBM SPSS version 22.0 statistical software (SPSS Inc., Chicago, IL, USA).

Normal distribution and equality of variance will be assessed before any statistical analysis using the Kolmogorov-Smirnov test.

A descriptive analysis will be performed with mean, standard deviation, minimum and maximum values. For variables with a non-normal distribution, the median will be used as a measure of centralization, and the 25 and 75 percentiles as measures of dispersion.

Absolute and relative frequencies will be given for qualitative variables.

For quantitative data, comparisons between two means will be made using Student’s t-test or Mann-Whitney U-test. Pearson’s Chi2 test and Fisher’s exact test will be used to compare percentages.

The significance level will be set at 0.05.

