**Fig 1 pone.0300250.g001:**
[figure not shown]
The schedule of enrolment, interventions, and assessments *. *Recommended content can be displayed using various schematic formats. See SPIRIT 2013 Explanation and Elaboration for examples from protocols. **List specific timepoints in this row.

Patients will be included in the study if they: (a) are 18 years or older; (b) have a documented diagnosis of coronary heart disease including acute myocardial infarction (AMI) (Non ST and ST elevation MI), patients with unstable angina, and patients with stable angina; (c) have access to a computer, and (d) agree to participate.

The exclusion criteria include: patients who are (1) with a history of psychiatric and neurological disorders; (2) unable to speak or understand Arabic; (3) with impaired bilateral hearing, or visual impairment which limits the use of computers; (4) with contraindications or severe physical disabilities that limit patients from participation; Additional exclusion criteria will be applied if patients are not able to understand the procedure and the aims of the study after full explanation.

By using the results of a meta-analysis published in 2017 [5] for an incidence of a major cardiovascular event of 13.8% in the intervention group and 38.6% in the control group, with a power of 80% and a first-species risk α of 0.05, we found a size of 56 patients in each group.

All investigators in this study will attend rigorous training on data collection and research protocol.

Training sessions will be thorough, and detailed. The purpose of this rigorous training is to ensure that all investigators have a comprehensive understanding of the data collection methods and research protocols relevant to the study.

The research protocol encompasses the set of guidelines, procedures, and ethical standards that govern how the research study will be conducted. It includes considerations such as participant recruitment, informed consent, data handling, confidentiality, and data analysis methods.

These sessions will be held before the start of the survey to prevent measurement bias. In addition, all investigators are trained in the principles of therapeutic education.

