At the end of the TPE program, the medical team verifies eligibility for the digital platform program. A "therapeutic support" contract is signed by the program participant and the medical team, setting out the therapeutic objectives during follow-up, as well as the parameters to be collected and transmitted to the platform.

The TPE team will educate the patient in the use of the mobile application, which is based on the codes and uses of consumer applications.

*Second step: digital monitoring phase*

Every day, the patient will be invited to transmit the monitoring parameters set out in the "therapeutic support" contract.

Data will be transmitted asynchronously and securely on the monitoring platform.

*Third step: Data analysis phase*

The medical team can interact with the patient via the platform. If necessary, the patient can be called into the center by the medical team for reassessment and early consultation, in order to optimize his or her care pathway.

*Forth step: Assessment phase*

At 12 months, an assessment of knowledge retention will be carried out, as well as the incidence of major cardiovascular events.

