### Variable definitions

The American Heart Association defines the ideal cardiovascular health as simultaneous presence of four ideal health behaviors and three ideal metabolic indicators [17]. The four ideal health behaviors include nonsmoking, body mass index (BMI) < 25 kg/m2, physical activity at targeted level, and dietary consumption being consistent with current recommended guidelines. The three ideal metabolic indicators are identified as clinical parameters for blood pressure < 120/80 mm Hg, total cholesterol < 5.17 mmol/L (200 mg/dL) and fasting glucose < 5.60 mmol/L (100 mg/dL). Each component of the cardiovascular health metrics will be dichotomized as 1 (ideal status) or 0 (intermediate or poor status).

The validated Tunisian version of the SF-12 health survey (16) produces two summary scores: the Physical Component Summary (PCS) and the Mental Component Summary (MCS). These scores are standardized to have a mean of 50 in the general population, with a standard deviation of 10. Higher scores indicate better health-related quality of life.

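### The Kolmogorov-Smirnov test is named as the check of equal variance, which it cannot assess, so the equal-variance assumption of the listed Student's t-test has no valid stated check (minor; continuous secondary outcomes only)

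*Protocol article*

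**What the plan says.** All the relevant text is in the Data analyses section of the protocol article.

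- Preliminary checks: "Normal distribution and equality of variance will be assessed before any statistical analysis using the Kolmogorov-Smirnov test". One test is given for two different properties.
- Tests for quantitative data: "comparisons between two means will be made using Student’s t-test or Mann-Whitney U-test". No unequal-variance version is named, and no rule says when each test applies.
- The only written consequence of a non-normal result is descriptive: "For variables with a non-normal distribution, the median will be used as a measure of centralization", with the quartiles as the measure of spread.
- Level: "The significance level will be set at 0.05".

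Percentages, and so the primary outcome (occurrence of a major cardiovascular event), are compared by chi-square or Fisher's exact test. The continuous outcomes are secondary. The clearest are the two SF-12 summary scores, described under Variable definitions as standardised to mean 50 and SD 10. No other section names a test of variance or corrects the statement.

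**The concern.** A Kolmogorov-Smirnov normality test compares the shape of one distribution with a normal curve. When the mean and SD are estimated from the data, the scale cancels out: a normal sample with SD 20 looks the same to the test as one with SD 10. It cannot show that one arm is more variable than the other.

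Student's t-test pools the two variances. If they differ and the group sizes differ too, the pooled standard error is wrong. It is too small when the smaller arm is the more variable, and too large in the reverse case. The article shows that its authors meant to check this assumption but names a tool that cannot do so. This is a stated method that does not work, not a detail left for a fuller plan. At stake is the type I error of the comparisons of means among the secondary outcomes.

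**Working it through.** **The plan's own figure, and why it is not affected.** Inputs from the sample size paragraph (Settings and participants): 13.8% v 38.6%, power 80%, α 0.05. The mean proportion is 0.262 and the difference 0.248.

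- Uncorrected, two-sided: n = [1.96·√(2·0.262·0.738) + 0.8416·√(0.138·0.862 + 0.386·0.614)]² / 0.248² = (1.2189 + 0.5021)² / 0.0615 = 48.2, so 49.
- With continuity correction: (48.155/4)·[1 + √(1 + 4/(48.155·0.248))]² = 12.04·4.646 = 55.9, so 56.

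This matches the stated 56 per group. No variance assumption about a continuous outcome enters.

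**Does the named test respond to unequal variance?** Simulation with 3,000 trials per setting, normal data, 56 v 56, base SD 10 (the SF-12 reference SD). The SD ratios are assumptions. Rejection rates at 0.05:

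| SD ratio | K-S normality test | Two-sample K-S | Levene |
|---|---|---|---|
| 1 | 4.1% | 3.0% | 5.2% |
| 1.5 | 4.2% | 12.2% | 79.6% |
| 2 | 4.5% | 40.5% | 99.7% |
| 3 | 4.3% | 92.2% | 100% |

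The normality form, which is the natural reading, is flat. The two-sample form reacts to spread, but it also rejects 56.1% of the time for a pure mean shift of 0.5 SD with equal variances. It cannot separate unequal spread from a treatment effect.

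**What does this cost Student's t-test?** Let s₁ and s₂ be the true SDs.

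- Variance that the pooled test assumes: E = [((n₁−1)s₁² + (n₂−1)s₂²)/(n₁+n₂−2)]·(1/n₁ + 1/n₂)
- True variance: V = s₁²/n₁ + s₂²/n₂
- Type I error ≈ 2Φ(−1.96·√(E/V))

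*Planned numbers, 56 v 56.* E = (s₁² + s₂²)/56 = V, so √(E/V) = 1 and the error is about 5% whatever the SDs.

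*Unequal numbers.* These splits and SD ratios are assumptions, since the article gives neither.

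| n (smaller v larger) | SDs (smaller, larger arm) | E | V | √(E/V) | Type I error |
|---|---|---|---|---|---|
| 50 v 56 | 1.2, 1 | 0.0457 | 0.0467 | 0.990 | 5.2% |
| 45 v 56 | 1.5, 1 | 0.0623 | 0.0679 | 0.958 | 6.0% |
| 40 v 56 | 2, 1 | 0.0962 | 0.1179 | 0.904 | 7.7% |
| 50 v 56 | 1, 1.2 | 0.0467 | 0.0457 | 1.010 | 4.8% |
| 40 v 56 | 1, 2 | 0.1181 | 0.0964 | 1.107 | 3.0% |

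For example, in the third row: E = (39·4 + 55·1)/94 · (1/40 + 1/56) = 2.245·0.04286 = 0.0962, and V = 4/40 + 1/56 = 0.1179.

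Simulation with 100,000 trials or more per setting agrees to within about 0.2 percentage points: 5.2% and 7.7% at the two ends with the smaller arm more variable, and about 4.7–4.9% and 3.1–3.2% at the two ends in the reverse case. Welch's test stayed at about 5% throughout (4.8–5.1%).

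**The case against.** The case for leaving the text alone has force. Allocation is equal, both arms are to be followed for one year, and with 56 v 56 there is no distortion. The larger errors need both an appreciable imbalance and an SD ratio of 1.5 to 2, and nothing in the article suggests such a ratio for SF-12. At a ratio of 1.2, Student's t-test is at 5.2% for 50 v 56. SPSS, the named software, prints Levene's test and the unequal-variance result beside the pooled one, so an analyst could see the problem. All of this stands, and it keeps the point minor. It does not make the sentence right, and the article does not say which printed result would be used.

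A reader might infer more than the article supports:

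- *That a pre-test rule selects the test.* The order of the text hints at this, but the only written use of non-normality is for descriptive statistics.
- *That the pooled test would be used whatever the data show.* The article lists Mann-Whitney as well and does not say this.
- *That the platform entry check unbalances the arms.* The article says: "At the end of the TPE program, the medical team verifies eligibility for the digital platform program". That governs entry to the platform; nothing removes those who fail it from outcome assessment. Ordinary dropout could unbalance the arms, but no rate is given.
- *That the cardiovascular health score would always fail a normality test and so lose its mean difference.* Variable definitions says "Each component of the cardiovascular health metrics will be dichotomized" but states no sum, and Mann-Whitney is a valid choice for a short ordinal score.

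**Conclusion.** The statement is wrong as written: the named test cannot assess equality of variance between arms, and the article names no other check. The finding is minor. It reaches only comparisons of means among secondary outcomes. At the planned equal numbers the type I error of Student's t-test remains about 5%. A departure appears only if evaluable numbers and variances both differ. Under the assumed ranges (50 to 40 v 56; SD ratio 1.2 to 2) the error runs from about 5.2% to 7.7% with the smaller arm more variable, and from about 4.8% to 3.1% with the larger arm more variable. Those ranges illustrate sensitivity and do not forecast what this trial will see.

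**What to change.** In Data analyses, remove the statement that the Kolmogorov-Smirnov test assesses equality of variance. Name Welch's unequal-variance t-test in place of Student's t-test for comparing means, and report the mean difference with its 95% interval. Mann-Whitney may stay for clearly non-normal or short ordinal outcomes. It should not be treated as protection against unequal variance: with normal data, 40 v 56 and a doubled SD in the smaller arm, it rejected 7.7% of the time in the 3,000-trial simulation. Levene's test may be reported for description, but should not decide which result is used.

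The cost is a sentence or two of wording. SPSS already prints the unequal-variance result with each t-test, and Welch's test held about 5% when variances were equal, so the downside is negligible. The sample size and the primary analysis need no change.

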### Control group

The control group will receive the usual controls at the hospital. Patients of the control group will not receive the TPE program neither a digital monitoring.

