### Outcomes

#### Primary outcome

The primary outcome of this study is the occurrence of major cardiovascular events in the year following hospital discharge for the control group, and in the year following completion of the TPE program with digital follow-up for the intervention group.

The primary outcome is based on the occurrence of acute myocardial infarction, stable angina, coronary revascularization, stroke, hospitalized heart failure, or death attributable to any cardiovascular disease [15]. Information on the primary outcome will be systematically obtained through follow-up interview at 12 months and confirmed by reviewing patients’ medical records. If a patient dies during follow-up, this information will be obtained directly from patient’s family or confirmed by physician.

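### The stated chi-square/Fisher comparison of one-year percentages cannot use partial follow-up, so any patient lost before month 12 shifts an arm's event rate; time to first event would be the better primary analysis

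*Protocol article*

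**What the plan says.** The *Primary outcome* section of the protocol article defines a yes/no outcome over one year. For controls it is "the occurrence of major cardiovascular events in the year following hospital discharge for the control group"; for the other arm the period is "in the year following completion of the TPE program with digital follow-up for the intervention group".

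Ascertainment is described in the same section: "Information on the primary outcome will be systematically obtained through follow-up interview at 12 months", with confirmation from medical records. On deaths it says: "If a patient dies during follow-up, this information will be obtained directly from patient’s family or confirmed by physician". Among deaths, only "death attributable to any cardiovascular disease" is a component of the outcome.

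The *Data analyses* section gives one method for categorical outcomes: "Pearson’s Chi2 test and Fisher’s exact test will be used to compare percentages". The sentence does not name the primary outcome, but nothing else in the section fits it, and the sample size in *Settings and participants* is also a comparison of two incidences (13.8% and 38.6%, 56 per group). The *Intervention* section plans 112 patients in total, which is 2 × 56. Everyone is to be followed for one year with three data-collection points. No time-to-event method is mentioned.

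**The concern.** A comparison of two percentages needs a settled yes or no at 12 months for every patient in the denominator. Someone last known to be event-free at month 8 has eight months of information that the test cannot use. Dropping such patients while keeping leavers with a known event raises the arm's rate. Counting them as event-free for the whole year lowers it. If loss differs between arms, part of the estimated difference reflects retention and not treatment, and its sign depends on the rule used.

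Two features of this trial make the point practical. First, contact is uneven: intervention patients send data daily and can be messaged or called in, whereas for the other arm "Patients of the control group will not receive the TPE program neither a digital monitoring". Unequal retention is therefore plausible. Second, recruiting exactly 2 × 56 leaves no visible allowance for patients who cannot be classified at month 12.

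**Working it through.** **Inputs from the article.** Control rate 0.386, intervention rate 0.138, planned difference 24.8 points, power 80%, α 0.05, 56 per group. **Assumed, because the article does not give them:** the proportion lost (L), a constant event hazard, leaving times uniform over the year, leaving independent of event risk, and events before leaving being known.

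**The plan's own figure.** The two-sided two-proportion formula with pooled variance under the null is [1.96·√(2·0.262·0.738) + 0.8416·√(0.138·0.862 + 0.386·0.614)]² / 0.248² = 48.2. The continuity correction, (n/4)·[1 + √(1 + 4/(n·0.248))]², gives 55.9, so 56 per group. This reproduces exactly and supports reading the percentage comparison as the intended primary analysis.

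**Event probability in a leaver.** With h = −ln(1 − p), the mean probability of an event before a uniformly distributed leaving time is m = 1 − p/h.
- Control: h = 0.4878, m = 1 − 0.386/0.4878 = 0.2086.
- Intervention: h = 0.1485, m = 1 − 0.138/0.1485 = 0.0707.

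**Two ways to handle leavers.**
- Counted as event-free: A = (1 − L)·p + L·m.
- Event-free leavers dropped, known events kept: B = A / [(1 − L) + L·m].

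Example with 20% loss in controls and 5% in the intervention arm:
- Control: A = 0.80·0.386 + 0.20·0.2086 = 0.3505; B = 0.3505/0.8417 = 0.4164.
- Intervention: A = 0.95·0.138 + 0.05·0.0707 = 0.1346; B = 0.1346/0.9535 = 0.1412.

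| Loss, control / intervention | Counted event-free | Difference (points) | Dropped | Difference (points) |
|---|---|---|---|---|
| 5% / 5% | 37.7% vs 13.5% | 24.2 | 39.3% vs 14.1% | 25.1 |
| 10% / 10% | 36.8% vs 13.1% | 23.7 | 40.0% vs 14.5% | 25.5 |
| 20% / 20% | 35.1% vs 12.5% | 22.6 | 41.6% vs 15.3% | 26.3 |
| 20% / 5% | 35.1% vs 13.5% | 21.6 | 41.6% vs 14.1% | 27.5 |
| 5% / 20% | 37.7% vs 12.5% | 25.3 | 39.3% vs 15.3% | 24.0 |

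Differences are taken before rounding.

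**No true effect.** Assume a 25% rate in both arms and 20% control versus 5% intervention loss. Then h = 0.2877 and m = 1 − 0.25/0.2877 = 0.1310. Counting leavers as event-free gives 22.6% vs 24.4% (control minus intervention −1.8 points). Dropping them gives 27.4% vs 25.5% (+1.9 points). A false difference of about 2 points appears, in opposite directions.

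**Feasibility of a time-to-event analysis.** Under constant hazards, HR = 0.1485/0.4878 = 0.304. Events needed for 80% power: Schoenfeld 4·(1.96 + 0.8416)²/[ln 0.304]² = 22.2, so 23; Freedman (1.96 + 0.8416)²·[(1 + 0.304)/(1 − 0.304)]² = 27.6, so 28. Expected with full follow-up: 56·(0.138 + 0.386) = 29.3. With independent exponential dropout, 27.9 events are expected at 10% and 26.5 at 20%. Schoenfeld power is 90%, 88% and 86% at 0%, 10% and 20% dropout. By Freedman's stricter count, 20% dropout falls slightly short.

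**The case against.** The strongest reply is that the test fits the design. The outcome is occurrence within a year, follow-up is a fixed year for all, and the sample size compares two proportions. With complete follow-up, chi-square or Fisher is legitimate. That stands: a reader might infer that the stated test is invalid, and the article does not support this, since it neither states nor implies any loss.

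A reader might also infer that a non-cardiovascular death has no proper place in a percentage. It has. Only cardiovascular death is a component, so a patient known to have died of another cause without a prior event had no such event by month 12. Counting that patient as a non-event gives the correct crude cumulative incidence. Calling such a death a competing event only clarifies the estimand.

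A third tempting inference is that controls will be lost more often. Uneven contact makes unequal loss plausible, but all participants have three data-collection points, controls have usual hospital follow-up, and daily reporting could itself cause withdrawal in the intervention arm. The direction is not established. Medical records, and for deaths the family or physician, will also classify some patients who miss the interview.

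The size is limited too. Rates of 35.1% and 13.5% correspond to about 20/56 and 8/56, for which Fisher's test gives p = 0.015, so the conclusion would survive if the planned effect is real. Finally, the absence of a printed rule for leavers is no fault in an article, because such rules commonly sit in an analysis plan that is not shown. The point rests only on the method that is stated.

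**Conclusion.** The point holds in limited form. The stated comparison of percentages cannot use partial follow-up, and a better method is available at small cost. The distortion arises only for patients whose event status is unknown at month 12.

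The gap between the two handling rules is 0.9 points at 5% equal loss, 1.8 at 10%, 3.8 at 20%, and about 6 in the one unequal scenario of 20% control versus 5% intervention loss. These figures rest on assumed loss rates, a constant hazard and uniform leaving; the article gives none of them. The distortion is small beside 24.8 points, but would weigh more if the true effect is smaller than planned. The change is advisable; the stated test is not an error that invalidates the trial.

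**What to change.** Make the primary analysis time to first major cardiovascular event in all randomised patients. Measure it from randomisation in both arms, because the present definition starts the year at discharge in one arm and at completion of the education programme in the other, and a Kaplan-Meier or Cox analysis would inherit that mismatch. Censor at the last date on which event status is documented, or at 12 months. Report 12-month cumulative incidence by arm with the difference and its 95% CI, plus a log-rank or Cox comparison. State how non-cardiovascular death enters the estimand, for example as a competing event. Keep the chi-square/Fisher test as a sensitivity analysis.

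Cost: rewording the outcome and analysis sections, and taking event dates and last-contact dates from the records already to be reviewed. The article does not say that dates are recorded, so this must be added to data collection. The planned 112 patients can stay. If the percentage comparison remains primary instead, 56 evaluable patients per arm would need 63 enrolled at 10% loss (56/0.90 = 62.2) or 70 at 20% (56/0.80). Downside: censoring is assumed non-informative, and the sensitivity analysis is still needed for that reason.

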### Intervention

To identify eligible patients, a targeted review of patients’ medical record based on the inclusion and exclusive criteria will be carried out, with referrals from nurses or clinicians within the study site. During the formal screening session, we will ask patients to complete an initial screening assessment which includes age, educational background, diagnosis, heart function grade, etc. Patients who meet the study criteria will be asked to sign a written informed consent before attending the baseline visit. Participants’ baseline data includes patients’ general characteristics, health behaviors (daily diet, physical activities, smoking status) and medication adherence, as well as their blood pressure, blood glucose, blood lipid levels during hospitalization.

A total of 112 patients with coronary heart disease will be recruited at a clinical site and divided equally into an intervention group and a control group. All participants will be followed up for a total of one year (with three time-points for data collection).

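### The only test stated for event percentages ignores the baseline diagnosis already recorded; one pre-specified stratifier would be a cheap improvement, though the crude test is valid and adequately powered

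*Protocol article*

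**What the plan says.** - **Test.** In the Data analyses section, Student's t-test or the Mann-Whitney test compares quantitative data. For proportions there is Pearson's chi-square, and Fisher's "exact test will be used to compare percentages". No stratified or covariate-adjusted analysis is named, and no test is tied to the primary outcome by name.
- **Outcome.** Under Primary outcome: "The primary outcome of this study is the occurrence of major cardiovascular events in the year following hospital discharge for the control group", with a corresponding one-year window for the intervention group. It is binary per patient.
- **Patients.** Settings and participants admits "acute myocardial infarction (AMI) (Non ST and ST elevation MI), patients with unstable angina, and patients with stable angina".
- **Baseline data.** The Intervention section describes an "initial screening assessment which includes age, educational background, diagnosis, heart function grade" and other items. Screening comes before consent there, and Study design puts consent before randomisation, so both diagnosis and grade are fixed before allocation.
- **Size.** Rates of "13.8% in the intervention group and 38.6% in the control group", "with a power of 80% and a first-species risk α of 0.05", and "we found a size of 56 patients in each group". The 112 patients are "divided equally into an intervention group and a control group". The article mentions random assignment but describes no method and no stratification.

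**The concern.** The trial pools several presentations of coronary disease, and risk over the following year may well differ between them. With 56 per group and no stratification described, the arms can differ by chance in index presentation, and a crude two-by-two test then mixes that difference with the treatment effect. Using a baseline factor in the analysis removes this part and usually gains a little power from the same patients.

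Credibility is also at stake. With about 29 expected events, a visible imbalance in diagnosis would invite challenge to the main result, and an adjustment chosen after the data are seen would look selective.

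**Working it through.** **1. Reproduce the planned size.** Inputs from Settings and participants: p1 = 0.138, p2 = 0.386, difference d = 0.248, mean 0.262, α = 0.05 (taken as two-sided), power 80%.

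n = [1.96·√(2·0.262·0.738) + 0.842·√(0.138·0.862 + 0.386·0.614)]² / 0.248² = (1.219 + 0.502)² / 0.0615 ≈ 48.2, so 49 without continuity correction.

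With continuity correction: (48.2/4)·[1 + √(1 + 4/(48.2·0.248))]² ≈ 55.9, so **56**. The stated figure reproduces.

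**2. Power of the stated tests at 56 per group**, by exact enumeration of both binomials: Pearson 86.6%, Fisher 81.5%. Both exceed 80%.

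**3. Expected events.** 56·0.138 + 56·0.386 = 7.7 + 21.6 ≈ 29.

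**4. Chance imbalance.** Two independent binomials of size 56, which assumes unstratified allocation. The factor's prevalence is assumed.

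| Prevalence | Gap ≥ 10 points | Gap ≥ 15 points |
|---|---|---|
| 30% | 26% | 8% |
| 50% | 30% | 11% |

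**5. Shift in the crude risk difference.** It equals the imbalance times the risk gap between factor levels. At an overall risk of 26.2%:
- Odds ratio 2, prevalence 50%: level risks about 19.6% and 32.8%, so 10 points of imbalance shift the difference by 0.10·13.2 ≈ 1.3 points.
- Odds ratio 5, prevalence 30%: level risks about 16.3% and 49.3%, so the shift is 0.10·33.0 ≈ 3.3 points.

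**6. Crude v stratified test, by simulation** (at least 200,000 trials per setting, 56 per group, prevalence 30% or 50%). In stratum k, with arm sizes n1k and n0k, total Nk, total events mk and intervention events ak, the CMH statistic without continuity correction is

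[Σ(ak − n1k·mk/Nk)]² / Σ[n1k·n0k·mk·(Nk − mk) / (Nk²(Nk − 1))], compared with 3.84.

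Power at 13.8% v 38.6%:

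| Assumed odds ratio of the factor | Pearson | CMH |
|---|---|---|
| 1 | 86.4-86.5% | 86.0-86.1% |
| 2 | 86.6% | 86.8% |
| 3 | 86.6% | 87.7-87.9% |
| 5 | 86.5-86.7% | 89.3-89.7% |

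Type I error at 26.2% in both arms, in trials with an imbalance of 15 points or more:

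| Assumed odds ratio | Pearson | CMH |
|---|---|---|
| 2 | 5.7-5.8% | near 5% |
| 3 | 7.0-7.4% | near 5% |
| 5 | 8.9-10.1% | near 5% |

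Over all trials, both tests hold about 5%.

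**7. Richer adjustment.** A logistic likelihood-ratio test with infarction yes/no plus a linear grade gave type I error of 5.1-6.0%. With all categories of both factors it gave 5.4-6.5%, at about 29/7 ≈ 4 events per parameter (six covariate terms plus treatment). These runs used 4,000 trials per setting. They argue for one factor only.

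**The case against.** **The crude test is correct.** Under randomisation it is valid, it matches the sample-size calculation, and it exceeds the target power. This stands. A reader might infer that the primary analysis is wrong or underpowered; the documents do not support that.

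**The conditional error rates are selective.** If the error is 7.0% in 11% of trials and 5.0% overall, the remaining 89% run at (5.0 − 0.11·7.0)/0.89 ≈ 4.75%. This stands as a caution: the 6-10% must not be read as the test's type I error. The 11% is also the 50%-prevalence case; at 30% it is 8%. A shift of 1.3 to 3.3 points per 10 points of imbalance is small beside the planned 24.8-point difference.

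**The article is a summary.** Data analyses never names the primary test, and an adjusted analysis or a stratified allocation could sit in a document not shown. In part this stands. A reader might infer that allocation is unstratified, but the article only leaves the method undescribed, so the imbalance figures are conditional on that reading. The point does not depend on silence alone, however: the section lists its between-group tests, and all are unadjusted.

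**Adjustment is not free.** This stands for multi-term logistic models, which were slightly liberal. It does not apply to one binary stratifier, whose CMH test stayed near 5%. Even there, a non-prognostic factor costs a little power.

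**The stratifier is a judgement.** Stable angina is both an entry diagnosis and a component of the primary outcome, so the direction of its association with events is unclear. That is fair, but a stratified test needs only a difference in risk, in either direction. Its size remains unknown.

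**Conclusion.** The point holds as a missed, inexpensive improvement. The expected benefit is about 0 to 3 points of power for one binary factor with an odds ratio between 2 and 5. The stratified test also protects against chance imbalance in the 8-11% of trials where the gap reaches 15 points. The downside is about 0.4 points of power if the factor is not prognostic.

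The size rests on three assumptions that the documents do not settle: the prognostic strength of index presentation, a prevalence of 30-50% for the smaller category, and allocation not stratified by diagnosis. A rarer category or a weaker factor would bring the gain close to zero. The firmest reason to act is that the choice is made before the data are seen.

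**What to change.** In Data analyses, name the primary test: a Cochran-Mantel-Haenszel test stratified by index presentation at screening, with acute coronary syndrome (myocardial infarction or unstable angina) against stable angina. State that it is used without continuity correction, the form to which the figures above apply. Report the stratified risk difference, weighted by n1k·n0k/Nk, with its 95% interval. Keep the crude test as supportive, and use heart function grade in a sensitivity analysis only. If the investigators prefer a different two-way split of diagnosis, they should fix it before any outcome data are seen.

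The cost is two or three sentences. The diagnosis is already collected, the planned software can run the test, and the sample size need not change. One factor must be committed to in advance.
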